### Sample size

2.9

This study is a RCT, and the diopter of the research object is the main observed outcome index. According to previous literature reports, it is estimated that the mean diopter of experimental group 1 is -1.52, the standard deviation is 0.87, and the diopter of experimental group 2 is- 1.81, the standard deviation is 1.25. Set α = 0.25 (2-sided) and β = 0.10. We use PASS 15 software (PASS 15.0.5 NCSS, LLC USA) to calculate the experimental size of the test group and the control group N1 = N2 = N3 = 74 cases. Assuming that the loss to follow-up rate of the study subjects is 20%, the sample size is N1 = N2 =  = N3 = 74÷0.8 = 93 cases. Therefore, the minimum sample size included in this study is 279 cases. In the actual study, a total of 300 cases will be included.

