### Statistical analyses

2.16

Data analyses will be processed with SPSS 22.0 (SPSS Inc., Chicago, IL) and supervised by a skilled statistician blinded to group allocation.

The Full Analysis Set (FAS) is for all participants who have been randomized in terms of the intention-to-treat (ITT), and the per-protocol analysis set (PPS) and is for the individuals who complete the trial and do not have significant protocol violations. On the basis of rule of the last-observation-carried-forward, missing values will be imputed. In order to evaluate therapeutic effect and safety, the FAS and PPS will be used simultaneously.

Categorical data, such as gender and medical history, will be tabulated with frequencies or percentages; and continuous data, such as age and disease course, will be reported as mean ± standard deviation (SD), or median. For the baseline variables, sociodemographic data and other basic indicators will be carried out using analysis of variance (ANOVA) and χ^2^. To compare variables before and after treatment in the same group, a paired *t* test will be used. Repeated-measures ANOVA will be used to compare the intergroup differences among the 3 groups. Tests of ITT between the acupuncture with the deqi group and acupuncture without the deqi group arms and between the acupuncture withou the deqi group and waiting-list group arms with respect to the change will based on time-intervention interactions in the mixed-effect models. A *P* value of less than .05 (2-sided) indicates a statistically significant difference, with 95% confidence intervals.

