## Discussion

3

Currently, there have been no methodologically controlled clinical studies confirming the efficacy of acupuncture therapy in the treatment of myopia. To meet the demand for high-quality RCTs, our team has designed this randomly controlled trial to explore the potential therapeutic effect of acupuncture on myopia. In this pilot study, we will compare the change in diopter of 3 interventions: acupuncture Deqi, acupuncture without Deqi and waiting list. This 3-arm RCT aims to investigate the relative contributions of the specific (acupuncture Deqi vs acupuncture without Deqi) and the nonspecific (acupuncture without Deqi vs waiting list) effects to the overall clinical effects of the acupuncture Deqi on adolescents with myopia. In particular, a growing body of studies has confirmed that the importance of Deqi, having Deqi, and no Deqi has a huge impact on the experimental structure.

For the purpose of comparing the nonspecific (sham intervention vs no treatment) effects and avoiding bias caused by psychological influences, we set the third group of the waiting-list control without any acupuncture interventions. This is because participants in the acupuncture with the deqi group may have a placebo effect due to the unawareness of group allocation and the treatment that they are undergoing; therefore, placebo effects may happen secondary to their strong beliefs of being in the acupuncture with the deqi group.

To our knowledge, the present study will be the first clinical trial that compares acupuncture Deqi with acupuncture without Deqi, and being placed in a waiting list control group in treating myopia. The scientific and rigorous methodological design of this trial hopefully will provide consolidated evidence on the efficacy and safety of the acupuncture Deqi for treating myopia, and hopefully provide reference to clinical practice Additional file.

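### Section 2.9 implies 90% power for three arms from one 0.29 D difference tied to no contrast; on a level comparison the printed inputs deliver it for neither contrast tested in section 2.16

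*Protocol article*

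**What the plan says.** Section 2.9 (Sample size) names diopter as the main outcome and takes its inputs from unnamed earlier publications. For one group it assumes that "the mean diopter of experimental group 1 is -1.52, the standard deviation is 0.87". The values for the other group read "the diopter of experimental group 2 is- 1.81, the standard deviation is 1.25". The error rates are given as "Set α = 0.25 (2-sided) and β = 0.10". PASS 15 is then used to "calculate the experimental size of the test group and the control group N1 = N2 = N3 = 74 cases". Allowing 20% loss, 74 becomes 93 per arm and 279 in total; 300 will be enrolled, which at 1:1:1 (section 2.10) is 100 per arm.

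The two groups are called experimental group 1 and 2 when the means are given, and test and control group when the size is given. Neither pair of labels is mapped to the three arms, and no third mean is given.

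Section 2.16 (Statistical analyses) plans two pairwise comparisons through time-by-intervention interactions in mixed models. The first is "Tests of ITT between the acupuncture with the deqi group and acupuncture without the deqi group arms"; the second compares acupuncture without Deqi with the waiting list. Significance is two-sided 0.05. Section 3 (Discussion) describes the aim as estimating "the relative contributions of the specific (acupuncture Deqi vs acupuncture without Deqi) and the nonspecific (acupuncture without Deqi vs waiting list) effects".

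**The concern.** The sample size section implies a property of the design: 90% power with 74 evaluable adolescents per arm. Two pairwise tests lean on it, but only one difference was assumed, and the text does not say which test it belongs to. The contrast that it does not describe has no power statement at all. The alpha used for sizing (0.25) also differs from the alpha used for testing (0.05).

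The Deqi contrast is the trial's main question (section 1). If true power is far below 90%, a non-significant result on that contrast is weak evidence, and a reader who trusts section 2.9 would give it too much weight.

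**Working it through.** **Inputs.** From section 2.9: means -1.52 and -1.81, so d = 0.29 D; SDs 0.87 and 1.25; alpha 0.25 two-sided; power 0.90; 20% loss; 300 enrolled. From section 2.16: alpha 0.05 two-sided. Evaluable n at N = 300: 100 per arm, or 100 × 0.8 = 80 after loss.

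**Step 1: the plan's own figure.** For two means with equal n,

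n = (z₁₋α/₂ + z₀.₉₀)² × (0.87² + 1.25²) / d²

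0.87² + 1.25² = 0.7569 + 1.5625 = 2.3194, and 2.3194 / 0.29² = 27.58.

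- Alpha 0.25: (1.150 + 1.282)² × 27.58 = 163.1, so 164 per arm (Welch t: 164).
- Alpha 0.05: (1.960 + 1.282)² × 27.58 = 289.8, so 290 per arm (Welch t: 291).

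The stated 74 is not reproduced. Reading alpha as a misprint for 0.025 does not help: that needs 343 per arm two-sided, or 290 one-sided. Among the two-group variants tried at 90% power, the nearest was 69, with SD 0.87 alone and one-sided alpha 0.25. The loss step is correct: 74 / 0.8 = 92.5, rounded to 93, and 3 × 93 = 279.

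**Step 2: power for 0.29 D.**

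Power = Φ(d/SE − z) + Φ(−d/SE − z), with SE = √(2.3194/n) and z = z₁₋α/₂.

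- n = 74: SE = 0.177, d/SE = 1.638. Power is 69% at alpha 0.25 and 37% at 0.05.
- n = 80: SE = 0.170, d/SE = 1.703. Power at 0.05 is Φ(−0.257) = 40%.
- n = 100: SE = 0.152, d/SE = 1.904. Power at 0.05 is Φ(−0.056) = 48%.

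At alpha 0.05, the difference detectable with 90% power is 3.242 × SE: 0.49 D at 100 per arm and 0.55 D at 80.

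**Step 3: if 0.29 D were the overall effect.** This is an assumption. The overall Deqi versus waiting-list effect is the sum of the two tested components. If both act in the same direction and sum to 0.29 D, at least one is 0.145 D or less. The shares below are illustrative; the documents give no split. Power at two-sided 0.05:

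| Effect on a tested contrast | 100 per arm | 80 per arm |
|---|---|---|
| 0.29 D (whole) | 48% | 40% |
| 0.193 D (two thirds) | 25% | 21% |
| 0.145 D (half) | 16% | 14% |
| 0.097 D (one third) | 10% | 9% |

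**The case against.** **The stronger reading.** A reader might infer that 0.29 D must be the whole acupuncture-versus-control effect, so that the power claim cannot hold for both tested contrasts. The argument is that section 3 says "the present study will be the first clinical trial that compares acupuncture Deqi with acupuncture without Deqi", so no literature value for that contrast could exist. The documents do not support this. The sentence goes on to include the waiting-list arm, so the novelty claimed may be the three-arm comparison. The source is given as reports in the plural, so the two means may come from separate studies. The experimental group labels fit two acupuncture arms at least as well as acupuncture and a waiting list. If 0.29 D is the Deqi contrast, the second contrast could also be 0.29 D or more; its power is then unsupported, not impossible.

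**One key contrast is enough.** Sizing a three-arm trial on one contrast and setting the arms equal is ordinary practice. That stands as a design choice. It does not rescue the figure, because 0.29 D does not reach 90% on whichever contrast it is assigned to.

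**A three-group calculation.** A reader might suppose that 74 came from a one-way ANOVA with an unprinted third mean. At alpha 0.25 and 90% power, third means of -1.81 and -2.10 give 152 and 51 per arm, so some value between them would give 74. But no third mean is stated, and such a calculation would power the overall test, not the two pairwise ones.

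**Levels versus change.** Section 2.16 tests change through an interaction, and the SD of change is not given. This stands, and it limits the conclusion. Taking a simple change score at 80 per arm and two-sided 0.05, 90% power for 0.29 D would need an SD of change of 0.29 × √40 / 3.242 = 0.57 D. With an SD of 1.077 (the root mean square of 0.87 and 1.25) at both times, that means a within-subject correlation of 1 − 0.57²/(2 × 1.077²), about 0.86. The planned test could therefore do better than the level figures, but section 2.9 makes no such argument and prints only level SDs.

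**Conclusion.** The concern holds in a limited form. The sizing rests on one difference that is tied to no contrast, while two contrasts are tested. On its own inputs the implied 90% is not reached for a 0.29 D effect on either: the shortfall is 164 or about 290 needed per arm against 74 stated, and 48% or 40% power at the enrolled size under the alpha actually used.

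These figures assume a two-group comparison of levels with the printed SDs. An effect of about 0.49 to 0.55 D on a contrast would reach 90%, but the plan assumes no such effect. The 16% and 14% apply only if 0.29 D is the overall effect and both components act in the same direction. That the power claim is impossible for both contrasts together is not established, and neither is the true power of the interaction test.

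**What to change.** In section 2.9:

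- State which two arms the means -1.52 and -1.81 represent, and so which contrast 0.29 D stands for.
- Replace the 90% claim with recomputed power at N = 300 (100 per arm, 80 after 20% loss) at two-sided 0.05, separately for Deqi versus without Deqi and for without Deqi versus waiting list, with an explicit assumed effect for each. If the effect is 0.29 D, the level-comparison entries are 48% and 40%.
- Say that these are level-comparison figures because the SD of change is not given. If the sponsor has an SD of change, use it and print it.

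The cost is a recalculation and a few sentences. No extra patients are needed and the tests in section 2.16 do not change. The stated power becomes less favourable.

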### Randomization and allocation concealment

2.10

Central random system is used to realize random grouping and random hiding of hierarchical blocks. This study is stratified according to the subcenter, randomly divided into acupuncture Deqi group, acupuncture without Deqi group, and waiting list group at a ratio of 1:1:1. A statistician from Sichuan Evidence-based Medicine Center of Traditional Chinese Medicine will use SAS 9.2 software (SAS, Cary, NC) to generate random sequences in 3 rounds of random sentences, list the random code tables corresponding to the serial numbers 001–300, and generate treatment assignments for 300 subjects. This process is implemented by the online central random system. The researcher enters the screening information of the prospective subjects on the central random system and obtains the subject number. After meeting the subject's criteria and signing the informed consent form, they are randomly divided into groups, and the random number is generated. Examiners and researchers cannot foresee the grouping information of the subjects, and the random number is managed by Sichuan Evidence-based Medicine Center of Traditional Chinese Medicine. Until the end of the study, the subjects, clinicians, and outcome measurers did not know the grouping of subjects.

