### Recruitment strategies

2.3

The trial will take place at the Teaching Hospital of Chengdu University of Traditional Chinese Medicine (TCM), China. Through flyers and social media advertisements, participants with myopia will be recruited from the Elementary School near the Chengdu University of Traditional Chinese Medicine. The subjects will be informed of the details regarding the trial plan and those who voluntarily participate in the trial will receive free ophthalmologic examinations. All participants or their guardians have the right to participate or drop out at any time, and will be required to sign the informed written consent before any study procedures.

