### Inclusion criteria

2.6

Patients with myopia who meet the following inclusion criteria will be enrolled in the trial:

(1)Age of 7∼16 years;(2)Meet the diagnostic criteria of myopia;(3)Agree to sign an informed consent form and volunteer for the research.

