### Blinding

2.11

This study uses a single-blind method. Acupuncture and acupuncture pseudo-acupoints will be performed by the same professional acupuncturist in the outpatient department according to uniform standards. All examinations will be checked and evaluated by the same doctor. The subjects will not know the specific grouping situation. Outcome evaluation and data statistics are performed by a third party who is not involved in the treatment. Only in emergency situations, such as a serious adverse event (AE), or when the subject needs emergency rescue, the researcher will report to the supervisor and the principal investigator to decide whether to unblind. Once the subject is unblinded, the case will be regarded as a drop-out case and will not be included in the efficacy analysis. However, if there is an adverse reaction, it should be included in the adverse reaction analysis, and the unblinding should be recorded in the Case Report Forms (CRFs) “Early Subject Exit Page” Related information, including the time of unblindness, reason, treatment, and treatment status.

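### The only stratification factor is a subcenter in what reads as a one-hospital trial, and the between-group analysis uses baseline diopter only as a repeated measure, not as a covariate, and names no age term

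*Protocol article*

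**What the plan says.** **Allocation.** Randomization and allocation concealment (2.10) describes a central system with stratified blocks ("Central random system is used to realize random grouping and random hiding of hierarchical blocks"), names one factor ("This study is stratified according to the subcenter") and allocates the three arms equally ("waiting list group at a ratio of 1:1:1"). It describes a single code list ("list the random code tables corresponding to the serial numbers 001–300").

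**Site.** Recruitment strategies (2.3) names one hospital: "The trial will take place at the Teaching Hospital of Chengdu University of Traditional Chinese Medicine (TCM), China". Under Blinding (2.11), needling in both acupuncture arms "will be performed by the same professional acupuncturist in the outpatient department according to uniform standards", and one doctor does all examinations. No subcenter is defined anywhere.

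**Population and outcome.** Eligibility covers "Age of 7∼16 years". Diopter is measured before treatment and at 1, 2, 3, 6, 9 and 12 months (2.12.5), which makes seven visits including baseline.

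**Analysis.** Statistical analyses (2.16) states: "Repeated-measures ANOVA will be used to compare the intergroup differences among the 3 groups". Its next sentence tests Deqi against non-Deqi, and non-Deqi against waiting list, on change, through time-by-intervention interactions in mixed-effect models. Neither sentence names a covariate.

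**The concern.** Two things look wrong. First, a stratum that exists at only one site has one level. The blocks still keep arm sizes equal, but the stratification adds nothing, and the text contradicts itself on how many sites there are.

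Secondly, the planning SDs (0.87 and 1.25 D) are large beside the planned difference of 0.29 D, so how the analysis handles between-child spread decides much of its power. A group main effect in a repeated-measures ANOVA handles it poorly. It averages in the baseline visit, where no effect can exist, and keeps the spread between children in its error term. The change test removes part of that spread, but less than a covariate would. At stake is precision that could be had without recruiting more children.

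**Working it through.** **Inputs.** From Sample size (2.9): means −1.52 and −1.81 D, so δ = 0.29 D; SDs 0.87 and 1.25 D; 300 children, or 100 per arm; 20% loss, so 100 × 0.8 = 80 completers per arm. From 2.16: two-sided 0.05.

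**Assumptions.** The planning SDs hold at baseline and at follow-up. The document gives no correlation ρ between baseline and follow-up diopter, so ρ is shown from 0.5 to 0.9. Power uses the normal approximation.

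**The plan's own figure.** The stated 74 per arm does not follow from the stated inputs. With n = (0.87² + 1.25²)(z₁₋α/₂ + z₀.₉₀)²/0.29², the result is 164 at the stated α of 0.25 and 290 at 0.05. The dropout step is right: 74/0.8 = 92.5, rounded up to 93, and 3 × 93 = 279. That mismatch is a separate matter. The steps below use only the SDs, δ and planned numbers.

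**Step 1: change analysis against baseline adjustment.** SE of a difference in single post-treatment values = √[(0.87² + 1.25²)/80] = √(2.3194/80) = 0.170 D. The variance is multiplied by 2(1 − ρ) for change and by 1 − ρ² for adjustment. The ratio is (1 + ρ)/2, so adjustment saves (1 − ρ)/2. Power ≈ Φ(0.29/SE − 1.96).

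| ρ | Change factor | Adjusted factor | Variance saved | Power, change | Power, adjusted |
|---|---|---|---|---|---|
| 0.5 | 1.00 | 0.75 | 25% | 39.9% | 50.3% |
| 0.7 | 0.60 | 0.51 | 15% | 59.4% | 66.5% |
| 0.8 | 0.40 | 0.36 | 10% | 76.8% | 81.0% |
| 0.9 | 0.20 | 0.19 | 5% | 96.8% | 97.4% |

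This takes the change test as one follow-up visit against baseline. A joint interaction test over all visits would give other figures. No gain is shown for age, because the document gives nothing from which to size it.

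**Step 2: the ANOVA group main effect, if that is the term tested.** Averaging seven visits of which six can carry an effect gives 0.29 × 6/7 = 0.249 D. Assuming equal correlation between all visits, the variance factor of the seven-visit mean is (1 + 6ρ)/7, which is 0.571, 0.743, 0.829 and 0.914 for ρ = 0.5, 0.7, 0.8 and 0.9. Power for a two-arm contrast at 80 per arm is then 48.9%, 39.5%, 36.1% and 33.3%. It falls as ρ rises, whereas both columns of Step 1 rise.

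**Step 3: chance imbalance.** At 100 per arm the SE of a baseline difference is √(2.3194/100) = 0.152 D. The chance that it exceeds 0.145 D is 34%, and that it exceeds 0.29 D is 5.7%. In a change analysis only (1 − ρ) of it carries over. A 1-SE imbalance leaves 0.076, 0.046, 0.030 or 0.015 D at ρ = 0.5, 0.7, 0.8 or 0.9.

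**Step 4: the stratum.** Section 2.10 implies at least two centres. Section 2.3 names one, and one acupuncturist and one examiner (2.11) fit a single site. Both descriptions cannot be right.

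**The case against.** The strongest reply is that 2.16 already uses baseline. Its pairwise tests concern change, and the pre-treatment diopter is one of the repeated measures. That stands. A reader might infer that the models ignore baseline refraction, or that adjustment would lift the planned test from 40% power to 81%. The document supports neither. The 40% belongs to an unadjusted comparison of post-treatment values, which is not the stated pairwise test; a change analysis equals it only at ρ = 0.5. Against a change analysis the gain is modest and almost vanishes at high ρ.

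It also stands that 2.16 does not say which ANOVA term is tested. The one-seventh dilution is therefore conditional and does not apply to the interaction tests.

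A reader might further infer that a one-level stratum, or the lack of strata for refraction and age, makes the randomisation invalid or the test biased. It does not. A one-level stratum reduces to ordinary blocked randomisation, and chance imbalance does not inflate type I error. Stratifying on prognostic factors is optional at 100 per arm, and a covariate list may be in an analysis plan that is not shown. The missing age term is thus a matter for recommendation, not an error.

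None of this resolves the conflict between 2.10 and 2.3, or makes the ANOVA sentence a good choice for the three-group comparison.

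**Conclusion.** The point holds in two parts. The subcenter stratum contradicts the single-site description and must be reconciled with it; if there is one site, it balances nothing and does no harm to validity. The between-group analysis is less efficient than it could be at almost no cost. Against a change analysis, baseline adjustment saves 5 to 25% of variance over ρ = 0.9 to 0.5, worth roughly 10 percentage points of power at ρ = 0.5, 7 at 0.7, 4 at 0.8 and under 1 at 0.9. The loss is much larger if the ANOVA group main effect is what is tested: 36.1% against 81.0% at ρ = 0.8. These figures rest on the planning SDs holding at both times, 80 completers per arm, an assumed ρ and, for the main effect, equal correlation between visits. This is an improvement worth making, not a threat to the trial's validity.

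**What to change.** 1. Reconcile 2.10 with 2.3 and 2.11. If there is one site, remove the subcenter stratum from the text. If there are more, name them and correct the single-site statements.
2. In 2.16, replace the unadjusted repeated-measures ANOVA and the change test with a mixed model of post-baseline diopter, with baseline diopter and age as covariates, and test the treatment contrasts at the stated visit or visits.
3. Optionally, stratify by baseline refraction and age, but only if recruitment has not started; 2.2 gives August 2020 as the start. Otherwise leave allocation alone and make only the changes above.

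The cost is wording. Both covariates are available at baseline, so no extra child, visit or measurement is needed. The optional strata would require refraction and age to be entered in the central system before randomisation.

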#### Acupuncture deqi group

2.12.2

On the basis of correction treatment with frame glasses, use acupuncture for acupoint treatment, specific as follows: the patient takes a sitting or supine position, selects eye acupuncture points (Sizukong, Tongziliao, Sibai), local skin and healers who left after routine disinfection 75% ethanol, with the sterile filiform needles (0.25 mm in diameter, 40 mm in length; Hwatuo, Suzhou, China), use both hands to insert the needle, flat puncture to deqi, lift and twist, 20 to 30 min/time.

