#### Acupuncture without deqi group

2.12.3

To avoid the deqi response, no needle manipulation will be performed after the perpendicular insertion. In order to reduce the bias caused by performance, all the rest of the clinical procedures remain the same.

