#### Waiting list group

2.12.4

No intervention will be performed in this group. The participants are required to continue their current living habits, including exercise and diet, while receiving free ophthalmologic examinations throughout the full observational period. To meet the requirements of the Rule of Ethics, all participants in the waiting list group will be offered free acupuncture treatment of their choice at the completion of the study.

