#### Primary outcome

2.12.5

The primary outcome will be diopter measurement of the patients before treatment, 1, 2, 3 months after treatment, and follow-up for 6 , 9 , and 12 months.

Full cycloplegia was obtained 45 minutes after administration of 1% cyclopentolate eye drops (15 mL; Alcon-Couvreur, Puurs, Belgium); Subsequently, the objective optometry (computer optometry and retinoscopy) was measured with a Topcon auto refractor KR8900 (Topcon, Tokyo, Japan); and then subjective optometrics. Subjective optometrics will be divided into the following 2 parts: optometrics will be conducted on a single eye (the right eye followed by the left eye), and a bilateral eye balance examination. Subjective optometrics of a single eye will be divided into the following 3 stages: the initial maximum plus the maximum visual acuity (MPMVA) will be identified, Jackson cross cylindrical lenses will be used to determine the axial direction and degree of the cylindrical lens, and the MPMVA will be repeated. The results will be recorded after optometrics. When the pupils recover, a re-examination will be carried out (3 days after the use of cyclopentolate hydrochloride eye drops). After re-examination, the glasses will be tried again. The degree of the glasses will be marked on the glass trial frame, to be chosen by the subjects based on subjective judgment. Finally, the diopter of the glasses and prescription glasses will be determined. The optometrist will not participate in other parts of the trial.

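### Blinding of subjects and clinicians is claimed where the waiting list and the acupuncturist cannot be blind; the claim should be narrowed and the primary diopter tied to one objective reading

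*Protocol article*

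**What the plan says.** **Blinding.** Section 2.10 (Randomization and allocation concealment) ends: "Until the end of the study, the subjects, clinicians, and outcome measurers did not know the grouping of subjects". Section 2.11 (Blinding) opens: "This study uses a single-blind method". It adds, with no exception for any arm: "The subjects will not know the specific grouping situation". It also assigns outcome evaluation and statistics to a third party outside treatment.

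**Who needles, and how.** Section 2.11: "Acupuncture and acupuncture pseudo-acupoints will be performed by the same professional acupuncturist in the outpatient department according to uniform standards". In the Deqi arm (2.12.2) the instruction is: "use both hands to insert the needle, flat puncture to deqi, lift and twist, 20 to 30 min/time". In the arm without Deqi (2.12.3): "To avoid the deqi response, no needle manipulation will be performed after the perpendicular insertion". For the waiting list (2.12.4): "No intervention will be performed in this group". Those children are offered free acupuncture only once the study is over.

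**Use of the arms.** Section 2.16 plans mixed-effects comparisons of Deqi against without Deqi, and of without Deqi against the waiting list. The Discussion presents the second as the nonspecific effect.

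**Primary outcome.** Section 2.12.5 names a diopter measurement and then describes several refraction steps. The last part includes: "The degree of the glasses will be marked on the glass trial frame, to be chosen by the subjects based on subjective judgment".

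**The concern.** Sections 2.10 and 2.11 describe different levels of blinding, and both assert more than the arms allow. A child who receives no needling for the whole study knows it. An acupuncturist who is told to manipulate the needle in one arm and leave it alone in the other knows the arm.

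A reader who relies on section 2.10 would take both planned contrasts as blinded for participants, but one of them is not. In that contrast, a measurement that depends on what the child reports can move with the child's knowledge of being treated or untreated, even when the person measuring is blind. Section 2.12.5 describes some readings that depend on the child's answers and some that do not, and does not say which is the primary value.

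**Working it through.** There is no planned figure to reproduce, so the check sets the sections side by side.

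**Step 1: numbers affected.** Section 2.10 allocates 300 subjects 1:1:1, so 300 / 3 = 100 per arm. That gives 100 children on the waiting list and 2 × 100 = 200 in the needling arms.

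**Step 2: each party's claimed and achievable status.**

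| Party | Section 2.10 | Elsewhere | What the arms allow |
|---|---|---|---|
| Children in the two needling arms (200) | Blind | Blind (2.11) | Possible: all are needled, and 2.12.3 keeps the other procedures the same |
| Children on the waiting list (100) | Blind | Blind, no exception (2.11) | Not possible: no needling until after the study |
| Acupuncturist | Blind, if counted as a clinician | Not listed as blind; one person treats both arms (2.11) | Not possible: insertion and manipulation differ (2.12.2, 2.12.3) |
| Outcome assessor | Blind | Third party (2.11), blinded (2.15) | Possible and supported |
| Statistician | Not mentioned | Third party (2.11), blinded (2.16) | Possible and supported |
| Optometrist | Not named separately | No other role in the trial (2.12.5) | Possible, but not stated outright |

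Section 2.11 speaks of pseudo-acupoints, which 2.12.3 does not describe. The table assumes that the sentence refers to the two needling arms.

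**Step 3: consequence for the planned contrasts.**

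- Deqi against without Deqi: participants can be blind; the acupuncturist cannot.
- Without Deqi against waiting list: participants cannot be blind. The three-group repeated-measures ANOVA in 2.16 also includes this open arm.

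**Step 4: candidate primary values in section 2.12.5, in order.**

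1. Objective refraction under cycloplegia (autorefractor and retinoscopy). It does not rest on the child's judgement.
2. Subjective refraction, right eye then left, followed by a binocular balance check. It depends on the child's answers.
3. Recording of the results.
4. Re-examination 3 days after the drops, then the trial frame and the child's choice. The choice depends on the child.
5. Determination of the power of the glasses.

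No step and no eye is named as the source of the primary value. Spherical equivalent appears in the exclusion criteria (2.7) but not in the endpoint. An objective reading is therefore available, but the text does not bind the analysis to it.

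**The case against.** **An open waiting list is inherent to this design.** Expectation is part of what needling against no treatment captures, and the Discussion talks openly about placebo effects from belief. This stands: the open arm is not a defect. What is wrong is the wording that says subjects in that arm do not know their group.

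**Section 2.10 may mean only allocation concealment, or examining doctors rather than the acupuncturist.** The sentence before it does concern foreseeing assignments. But the claim runs to the end of the study and covers clinicians without exception. Even the narrow reading leaves the waiting-list children, for whom section 2.11 repeats the claim.

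**The safeguards on measurement are sound.** Third-party evaluation, a blinded assessor, a blinded statistician and a separate optometrist are all stated. This stands and limits the harm. It does not protect a reading that rests on the answers of a child who knows the arm.

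**The reading and eye may be fixed in an analysis plan that is not shown.** This is fair, so leaving them open is not counted as an error in itself. Naming the reading is recommended because one contrast is open-label.

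**Stronger readings that the document does not support.**

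- A reader might infer that the primary value is the power chosen by the child. Results are recorded before the trial-frame step, and that step reads as dispensing the glasses that every arm receives. No section makes the chosen power the primary value.
- A reader might size the bias by setting one trial-lens step against the 0.29 D difference in section 2.9 (1.81 − 1.52 = 0.29). The step size is not in the document. One step in one child's reading moves a group mean by that amount only if nearly all children in an arm shift the same way. The 0.29 D also lies between two experimental groups, most naturally the needling arms, not the waiting-list contrast.
- A reader might infer that both eyes will be analysed as independent units, with an inflated type I error. Nothing says so: 2.9 counts cases and 2.16 defines the analysis sets by participants.
- A reader might apply the rule in 2.11 that removes unblinded subjects from the efficacy analysis to the whole waiting list. That rule concerns emergency unblinding.

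**Conclusion.** The blinding part holds with high confidence. Sections 2.10 and 2.11 disagree with each other, and both conflict with sections 2.12.2 to 2.12.4. The claim fails for 100 of the 300 children and for the acupuncturist who treats the other 200. One of the two contrasts named in the mixed-effects analysis is open-label for participants. Blinding of the assessor and statistician is supported and not in dispute.

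The endpoint part holds only in a limited form: the primary diopter is not tied to one reading, and subjective refraction is among the candidates. Whether this would bias the result depends on which reading is analysed, which the article does not say. No numerical size can be given. The point should be corrected, but it does not undermine the design.

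**What to change.** 1. Make sections 2.10 and 2.11 agree. Claim participant blinding only between the two needling arms. State that the waiting-list participants and the acupuncturist are not blind. State that the outcome assessor, optometrist and statistician are blind.
2. In section 2.16 and the Discussion, describe the comparison of acupuncture without Deqi against the waiting list as open-label for participants, and interpret it so.
3. In section 2.12.5, name one objective cycloplegic refraction already taken as the primary value, with one value per child by a stated eye rule. Autorefractor spherical equivalent is one example; retinoscopy, or a single named eye rather than a mean of both, would serve the same purpose. Keep subjective refraction and the power of the glasses as secondary or descriptive.

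**Cost.** No extra measurement is needed. The blinding claim becomes more modest. The SDs of 0.87 and 1.25 assumed in section 2.9 need a check against the chosen per-child value, since averaging two eyes, for example, can change the SD.
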